### Randomization

Patients will be randomly assigned to one of the two arms at a ratio of 1:1. The randomization list will be computer-generated by the study statistician using SAS system software (version 9.2, SAS Institute, Inc., Cary, NC, USA). The randomization process will be centralized through a secured website managed by the Bordeaux University Hospital Clinical Trial Unit (CTU) («Unité de Soutien Méthodologique à la Recherche Clinique et Epidémiologique (USMR)»). After confirmation of the patient’s eligibility criteria, the investigator will access the website of the CTU, which will provide the patient’s unique allocation number and randomization group. Access to the final dataset will be limited to the investigators.

### Determination of sample size

Sample size calculation was based on the noninferiority hypothesis that the prescription of short-course corticotherapy would be not less effective than partial endodontic treatment for reducing the pain caused by irreversible pulpitis in mandibular molars.

According to reported results [5], the proportion of patients showing successful relief (presenting pain <5 at 24 h on the NS) in the reference group (partial endodontic treatment) would be 95%. The noninferiority margin was defined as 20% fewer successes in the evaluated group (short-course corticotherapy). The calculation used Newcombe’s formula («lower confidence limit for difference in proportions (simulation)») for the procedure using the 6.0 version of NQuery software and resulted in a sample size of 40 patients per group to achieve 90% power and a one-sided type I error of 0.025.

However, to obtain satisfactory power, two features must be taken into account: (1) a slightly lower proportion of successful treatments in the evaluated group compared to the reference group (power of at least 80% if the treatment group were to have 3% fewer successes or at least 90% if it were to have 2% fewer successes,) and (2) a 5% proportion of patients lost to follow-up or randomly assigned to the corticosteroids group receiving the partial endodontic treatment before the first 24 h due to lack of efficacy [27]. Consequently, it was decided that 60 patients would be enrolled in each group, 120 in total.

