### Statistical analysis

The main analysis will be intention-to-treat (ITT) using the «missing = failure» strategy. A robustness analysis, supported by the per-protocol approach, will be carried out.

The difference between the two arms in the number of patients with pain <5 on the NS will be measured using its unilateral 97.5% confidence interval (CI) according to the binomial exact formula. The noninferiority hypothesis will be accepted if the lower confidence limit is superior to the noninferiority margin, which is fixed as −20%.

For qualitative outcomes, frequencies between the two groups will be compared using the chi-square test, or Yates’s corrected chi-square or Fisher’s exact tests, depending on the variables’ distributions. For quantitative outcomes, means will be compared using Student or Wilcoxon tests according to variables’ distributions. Regression model will be used to adjust on major confounding factors (i.e., age and sex). The statistical significance threshold will be 0.05.

Basic statistics in the study report will include information on missing values for all relevant study variables. A summary of baseline patient characteristics with totals and proportions (%) for categorical variables, and minimum, maximum, interquartile ranges and standard deviations for continuous variables will be presented. An estimation of primary and secondary outcomes will be calculated using their 95% CI.

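### The stated power of at least 90% at 2% fewer successes is about 86% if 5% of each arm are missing and scored as failures, as the main analysis requires

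*Protocol article*

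**What the plan says.** The Protocol article, Determination of sample size, starts from a success proportion that "in the reference group (partial endodontic treatment) would be 95" per cent. The margin is set as follows: "The noninferiority margin was defined as 20% fewer successes in the evaluated group". On the interval used for sizing, "The calculation used Newcombe’s formula", and this "resulted in a sample size of 40 patients per group to achieve 90% power and a one-sided type I error of 0.025".

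The section then names two reasons for going beyond 40. The first is a slightly lower true success rate on prednisolone: power should be at least 80% at 3% fewer successes and "at least 90% if it were to have 2% fewer successes". The second is a single 5% allowance that pools patients lost to follow-up with prednisolone patients who receive partial endodontic treatment within the first 24 h for lack of efficacy. The conclusion is that "it was decided that 60 patients would be enrolled in each group, 120 in total". How the 5% was turned into patients is not described.

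Under Statistical analysis: "The main analysis will be intention-to-treat (ITT) using the «missing = failure» strategy". Nothing there says how a rescued patient with a recorded 24 h score is classified.

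**The concern.** An attrition allowance normally assumes that lost patients leave the analysis, so the cost is a smaller sample with unchanged success rates. Here lost patients do not leave: they stay in the denominator as failures. That has two effects which a larger enrolment does not by itself repair. Success rates move away from 95% towards 90%, where the binomial variance is larger. And if losses differ between arms, the difference itself shifts towards the margin.

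At stake is the chance that a prednisolone regimen only 2 points worse than the reference is nevertheless not shown noninferior. The sponsor believes this risk is at most 10%.

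**Working it through.** **Inputs** (Determination of sample size; Statistical analysis): reference success 0.95; prednisolone success 0.93 (−2 points) or 0.92 (−3 points); margin −0.20; one-sided 0.025, so z = 1.96; 60 per arm; 5% allowance; missing = failure.

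**Method.** For x successes of n, with p = x/n, the Wilson limits l and u are [p + z²/2n ± z√(p(1−p)/n + z²/4n²)] / (1 + z²/n). With T for prednisolone and C for reference, the Newcombe lower limit is

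L = (p_T − p_C) − √[(p_T − l_T)² + (u_C − p_C)²].

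Power is the sum, over all pairs of counts, of the product of the two binomial probabilities wherever L > −0.20. This is full enumeration, not simulation.

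**1. The plan's own figures.**
- 40 per arm, 0.95 vs 0.95: 92.8%, consistent with the stated 90%.
- 60 per arm, no losses: 94.8% at −2, 90.9% at −3.
- 60 × 0.95 = 57 per arm, losses excluded: 93.5% at −2, 89.0% at −3.

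Both claims reproduce, with or without removing the 5% from n.

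**2. The planned main analysis.** Suppose each patient has a 5% chance of being missing, independent of outcome, and all 60 per arm are analysed:
- reference: 0.95 × 0.95 = 0.9025
- prednisolone at −2: 0.95 × 0.93 = 0.8835
- prednisolone at −3: 0.95 × 0.92 = 0.8740

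Power is **86.0%** at −2 and **81.0%** at −3.

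The reason shows in the simple standard error of the difference at −2. With 57 analysed and losses excluded it is √[(0.93×0.07 + 0.95×0.05)/57] = 0.044. With 60 analysed and losses failed it is √[(0.8835×0.1165 + 0.9025×0.0975)/60] = 0.056.

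Keeping 5% failed in each arm, about 67 per group would be needed to regain 90% at −2 (90.5%).

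**3. Sensitivity to the share scored as failure** (60 per arm, Newcombe, independent of outcome):

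| Scored as failure | −2 points | −3 points |
|---|---|---|
| 2.5% in both arms | 90.6% | 86.0% |
| 3% in both arms | 89.7% | 85.0% |
| 5% in both arms | 86.0% | 81.0% |
| 2.5% prednisolone only | 83.8% | 77.3% |
| 5% prednisolone, 2.5% reference | 78.0% | 71.4% |
| 5% prednisolone only | 67.0% | 59.2% |

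**The case against.** Several points on the other side have force.

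- **How the 5% was used is not stated.** A reader might infer that it was simply removed from n, since 57 per arm fits the claims. But 60 with no loss fits them too, so the text does not establish this. The point does not depend on it.
- **Rescue is not declared a failure.** The 24 h score is collected by telephone from every patient, so a rescued patient can have an observed value, and the missing-as-failure rule then does not apply. If all 5% were rescued patients with a recorded score and 95% success, power at −2 would be 95.1%.
- **Rescue overlaps with failure.** Rescues for lack of efficacy probably fall largely among the 7–8% of prednisolone patients already assumed not to succeed. Scoring those as failures costs no further power. A reader might infer from the last table row that the trial has only 67% and 59% power; that row needs all 5% to fall in one arm, independently of outcome, and the article supports neither condition. It is a worst case.
- **The pooled 5% may contain few missing outcomes.** With 2.5% missing in each arm, both claims hold.
- **The shortfall needs a varying number of losses.** With exactly 3 of 60 missing in each arm, Newcombe power at −2 is 91.6%. Chance imbalance in losses between arms is part of the 86%, but the trial cannot fix those numbers.
- **The 80% claim stands.** A reader might infer that both claims fail, since a score-based exact test gives 82.9% and 77.3% with 5% failed in each arm. Those figures partly reflect a separate mismatch: sizing used Newcombe, while the analysis specifies a "unilateral 97.5% confidence interval (CI) according to the binomial exact formula", whose ordering is not given.

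What remains is that the stated allowance, taken as 5% missing per arm under the stated rule, does not give the stated 90%.

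**Conclusion.** The point holds as a conditional one. Under the missing-as-failure rule, with 60 per arm, a 5% chance of a missing outcome in each arm unrelated to success, and the Newcombe limit used for sizing, power at 2 points fewer successes is about 86% rather than at least 90%: a type II risk of about 14% instead of at most 10%. The claim of at least 80% at 3 points fewer is met, narrowly, at about 81%.

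The 90% figure is safe only if fewer than about 3% per arm are scored as failures through loss. It worsens quickly if failures lean to the prednisolone arm, the only arm in which the rescue part of the 5% can arise: 2.5% there alone gives 83.8%. How far this applies cannot be settled from the article, because the split of the 5% and the scoring of rescued patients are not given. This is a misstatement of power; it does not show that the trial is too small to proceed.

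**What to change.** In Determination of sample size, restate power for the analysis that will be run: 60 per arm, all analysed, missing = failure. Give about 86% at 2 points fewer and about 81% at 3 points fewer if 5% per arm are missing independently of outcome. Add the one-sided cases as a sensitivity range, down to 67% and 59% if all 5% fall in the prednisolone arm, labelled as a worst case.

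State how the 5% divides between loss to follow-up and early rescue, how it entered the calculation, and how early-rescued patients with and without a 24 h score are counted in the main analysis.

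The cost is a rewritten paragraph and a less favourable stated power. Enrolment does not change.

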#### Outcomes

The primary outcome is the proportion of patients with pain intensity of below 5 on a Numerical Scale (NS <5) 24 h after the emergency visit [25]. The NS has already been used for the assessment of pain in previous studies to evaluate the efficacy of orally administered corticosteroids on pharyngitis presenting as an emergency [26]. Briefly, the patient will be asked to make a pain rating according to a NS score ranging from 0 to 10. A clinical research assistant will directly phone the patient and will use a standardized sentence: «Please indicate the intensity of your pain level on a scale of 0 (no pain) to 10 (worst pain imaginable)».

Secondary outcomes include:Number of analgesic drugs (step 1 on the World Health Organization analgesic ladder (paracetamol 1 g) or step 2 (paracetamol 600 mg/codeine 50 mg) taken after the inclusion visit up to 72 h)Difference in pain measured using the NS between T0 (baseline) and 24 h after the emergency visit (T1)Kinetics of pain, self-assessed using the NS at 6, 12, 24, 48 and 72 h after T0Patient’s comfort during complete endodontic treatment measured using the “Iowa Satisfaction with Anesthesia Scale” (ISAS) [23]Number of injected anesthetic cartridges required to achieve clinical silence for the realization of complete endodontic treatmentNumber of patients returning for the T2 visit

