### Protocol violations

All protocol violations occurring after randomization will be listed in the Clinical Study Report, tabulated by subject and recruitment site. The final assignment of participants to the per-protocol analysis will be decided at a blinded protocol violation review meeting before database locking.

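### A prednisolone patient who needs the comparator pulpotomy before 24 h can still be scored a prednisolone success, because neither the endpoint nor the failure rule takes account of rescue

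*Protocol article*

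**What the plan says.** Four sections of the protocol article bear on the point.

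- **Determination of sample size.** Part of the allowance is for patients "randomly assigned to the corticosteroids group receiving the partial endodontic treatment before the first 24 h due to lack of efficacy". They share a single 5% figure with losses to follow-up. Success in the reference arm is taken from reported results: the proportion "in the reference group (partial endodontic treatment) would be 95"%. On the margin: "The noninferiority margin was defined as 20% fewer successes in the evaluated group".
- **Outcomes.** "The primary outcome is the proportion of patients with pain intensity of below 5 on a Numerical Scale", assessed by telephone 24 h after the emergency visit. Nothing is said about treatment received in between.
- **Statistical analysis.** The main analysis is intention-to-treat, with a missing score counted as failure. In addition: "A robustness analysis, supported by the per-protocol approach, will be carried out".
- **Protocol violations.** "The final assignment of participants to the per-protocol analysis will be decided at a blinded protocol violation review meeting before database locking". No rule for rescued patients is given.

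**The concern.** The plan itself describes the event as a lack of efficacy of prednisolone, and the remedy is the treatment that prednisolone is meant to match. A rescued patient who answers the 24 h call has an observed score, so the missing-score rule does not apply. If the score is below 5, the relief may come from the pulpotomy, yet it is credited to prednisolone.

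In a noninferiority trial this makes the arms look more alike and so favours the claim. The Discussion presents prednisolone as a way to manage the emergency without partial endodontic treatment, and as something medical emergency services could give. A patient who needed the pulpotomy within a day does not support that use. The error would fall on the type I error of the primary conclusion.

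**Working it through.** **1. The plan's own sample size.** Inputs from Determination of sample size: 95% in both arms, margin 20 points, and "to achieve 90% power and a one-sided type I error of 0.025". Method: enumerate both binomial counts exactly and add up the probability that the Newcombe lower limit exceeds −20%.

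- 40 per arm: power 92.8% (87.2% with continuity correction). The stated 40 for 90% is reproduced closely enough.
- 57 evaluable per arm: 93.4% at 2 points fewer successes and 89.0% at 3 points fewer. This meets the stated 90% and 80%.
- 57 / 0.95 = 60 per arm, the stated final size.

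The last step treats lost or rescued patients as removed. The intention-to-treat analysis keeps all 60.

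**2. How a rescued patient is scored on the literal wording.**

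| 24 h call | Intention-to-treat result |
|---|---|
| Not reached | Failure (missing) |
| Score 5 or more | Failure |
| Score below 5 | Prednisolone success |

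Only the third row is a problem.

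**3. Effect on false noninferiority.** Assumptions: 60 per arm, the Newcombe one-sided 97.5% limit, reference success 95%, and 75% of prednisolone patients succeeding without rescue (95% − 20 points, exactly at the margin). Let r be the share of the prednisolone arm rescued before 24 h, drawn from the other 25%, and s the chance that a rescued patient scores below 5.

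Apparent prednisolone success = 0.75 + r × s. For example, 0.75 + 0.05 × 0.95 = 0.7975.

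| r | s = 0.50 | s = 0.95 |
|---|---|---|
| 2.5% | 3.8% | 5.5% |
| 5% | 5.8% | 11.4% |
| 10% | 12.2% | 36.2% |

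With rescue scored as failure the rate is 2.5% whatever r is.

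**4. If rescued patients were excluded from per-protocol.** Apparent success = 0.75 / (1 − r), with 60 × (1 − r) patients left in the prednisolone arm.

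- r = 5%: 0.75 / 0.95 = 0.789 with 57 patients; false noninferiority 9.1%.
- r = 10%: 0.75 / 0.90 = 0.833 with 54 patients; false noninferiority 27.4%.

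**5. One concrete result.** Newcombe lower limit = d − √[(p₁ − l₁)² + (u₂ − p₂)²], where d = p₁ − p₂, l₁ is the Wilson lower limit for prednisolone and u₂ the Wilson upper limit for the reference. Take 57/60 reference successes (p₂ = 0.950, u₂ = 0.983).

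- 48/60 on prednisolone (p₁ = 0.800, l₁ = 0.682): lower limit −27.2%, noninferiority not shown.
- 52/60 on prednisolone (p₁ = 0.867, l₁ = 0.758): lower limit −19.7%, noninferiority shown.

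Four rescued patients reporting a score below 5 separate the two conclusions.

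**6. Power if rescue is scored as failure.** Suppose 5% of the prednisolone arm is rescued, so that its success is 0.95 times what it would otherwise be, and the reference stays at 95%, with 60 per arm.

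| Prednisolone success otherwise | Success with rescue as failure | Power |
|---|---|---|
| 95% | 0.95 × 0.95 = 0.9025 | 81% |
| 93% | 0.93 × 0.95 = 0.8835 | 67% |
| 92% | 0.92 × 0.95 = 0.8740 | 59% |

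**The case against.** **The article may simply be silent.** Nowhere does it say that rescued patients count as successes. Because it groups them with losses to follow-up, the authors may have meant them to be treated as missing, hence as failures. The full protocol or an analysis plan, neither shown, may say so. That intention is possible, but it is not what the text provides. The endpoint and the failure rule are both stated here, and they yield a definite result for a patient with an observed score.

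**Not every rescue becomes a success.** A reader might infer that all rescued patients are credited to prednisolone. The wording does not support that: those with a score of 5 or more, or not reached, are failures. The 95% is also a figure for patients treated at the first visit. Rescued patients are treated later, after a first failure, and may do worse. This stands, and is why the results are given down to 50% relief.

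**Per-protocol exclusion is conjecture.** A reader might infer that the robustness analysis drops these patients. The document leaves membership to the review meeting and does not say so. This stands; the per-protocol figures are conditional on exclusion.

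**The rescue rate is unknown.** The plan's 5% also covers losses to follow-up, so 5% rescued is at the top of what it allows for, and 10% lies beyond it. This also stands.

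**The interval differs.** Statistical analysis names an exact binomial formula, whereas these results use the Newcombe limit from the sample-size section. The percentages would change somewhat with another interval. The direction would not, because apparent success rises with each credited rescue.

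**Intention-to-treat may properly ignore rescue.** A comparison of strategies including rescue is a legitimate question, but it does not answer whether prednisolone can replace the emergency pulpotomy.

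**Conclusion.** The point holds in limited form. The protocol foresees treatment failure that leads to the comparator before the primary assessment, and its endpoint and failure rule, as written, score such a patient as a prednisolone success whenever the 24 h score is below 5. Per-protocol would be biased the same way if these patients were excluded, which is plausible but not stated.

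The size depends on two inputs that the document does not give: the share rescued and the relief after rescue. Within the plan's 5% allowance (2.5% to 5% rescued, 50% to 95% relief), false noninferiority at the margin lies between 3.8% and 11.4% instead of 2.5%. The 36.2% figure needs both 10% rescued and 95% relief, so it is an upper illustration and not an expectation. The document does not support a claim that the sponsor intends to count failures as successes. It does support the statement that the rule as written allows it.

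**What to change.** In Outcomes and in Statistical analysis, state that a prednisolone-arm patient who received partial endodontic treatment before the 24 h assessment is a failure in the intention-to-treat analysis, whatever the score. State under Protocol violations that such a patient stays in the per-protocol set as a failure. Report the number of rescues by arm. Then bring Outcomes, Determination of sample size, Statistical analysis and Protocol violations into agreement, separating rescue from loss to follow-up in the 5% allowance.

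The wording change is a few sentences and does not alter patient care. The statistical cost is not trivial. Apparent prednisolone success falls, and the power statement must be restated with rescues as failures. At 60 per arm with 5% rescued, it is about 67% and 59% where the protocol now gives at least 90% and 80% (2 and 3 points fewer successes), and about 81% with success otherwise equal. The sample size should therefore be rechecked when the rule is settled, preferably before recruitment opens.

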### Statistical analysis

The main analysis will be intention-to-treat (ITT) using the «missing = failure» strategy. A robustness analysis, supported by the per-protocol approach, will be carried out.

The difference between the two arms in the number of patients with pain <5 on the NS will be measured using its unilateral 97.5% confidence interval (CI) according to the binomial exact formula. The noninferiority hypothesis will be accepted if the lower confidence limit is superior to the noninferiority margin, which is fixed as −20%.

For qualitative outcomes, frequencies between the two groups will be compared using the chi-square test, or Yates’s corrected chi-square or Fisher’s exact tests, depending on the variables’ distributions. For quantitative outcomes, means will be compared using Student or Wilcoxon tests according to variables’ distributions. Regression model will be used to adjust on major confounding factors (i.e., age and sex). The statistical significance threshold will be 0.05.

Basic statistics in the study report will include information on missing values for all relevant study variables. A summary of baseline patient characteristics with totals and proportions (%) for categorical variables, and minimum, maximum, interquartile ranges and standard deviations for continuous variables will be presented. An estimation of primary and secondary outcomes will be calculated using their 95% CI.

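### The primary noninferiority interval is called an exact binomial formula, but the trial was sized with Newcombe's interval; the name fixes no single method, and some readings miss the power targets

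*Protocol article*

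**What the plan says.** Protocol article, Determination of sample size: "The calculation used Newcombe’s formula", run as a simulation procedure in nQuery. The success rate assumed "in the reference group (partial endodontic treatment) would be 95"%, the margin is 20 points, and this "resulted in a sample size of 40 patients per group to achieve 90% power and a one-sided type I error of 0.025". Enrolment was then raised to 60 per arm for two reasons. One was to keep "power of at least 80% if the treatment group were to have 3% fewer successes" and "at least 90% if it were to have 2% fewer successes". The other was to allow for "a 5% proportion of patients lost to follow-up" or for crossing over to endodontic treatment before 24 h.

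Protocol article, Statistical analysis: the between-arm difference in patients with pain below 5 is to be "measured using its unilateral 97.5% confidence interval (CI) according to the binomial exact formula". Noninferiority is accepted if the lower limit lies above -20%. Nothing in the article links this interval to the one used for sizing.

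**The concern.** Newcombe's interval is a hybrid of two Wilson score limits. It is an approximation, not an exact method, so the two sections name different methods for the one quantity that decides the trial.

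The second name is also incomplete. An exact binomial interval is defined for a single proportion. For a difference of two independent proportions, several constructions can be called exact, and they are not equivalent: unconditional intervals ordered by a score statistic, unconditional intervals ordered by the raw difference, and combinations of two Clopper-Pearson limits. They differ in power and can give opposite decisions on the same data. If the choice were left until results were visible, it could settle the conclusion, and the protocol's power statements would belong to none of these exact methods.

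**Working it through.** **Inputs** (Determination of sample size; Statistical analysis). Reference success 95%; margin 20 points; one-sided 0.025; 40 per arm at first, 60 per arm finally; true differences of 0, -2 and -3 points, that is 95, 93 and 92% against 95%; 5% loss.

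**Method.** With x successes on corticotherapy, y on reference treatment and n per arm, every pair (x, y) is enumerated:

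power = sum over x, y of Bin(x; n, pT) × Bin(y; n, pR) × 1{lower limit(x, y) > -0.20}.

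One-sided error is the same sum with pT = pR - 0.20.

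**Step 1: the plan's own figures.** Newcombe's lower limit is d - sqrt[(p1 - l1)² + (u2 - p2)²], where d = p1 - p2, l1 is the Wilson lower limit for corticotherapy and u2 the Wilson upper limit for reference. At 40 per arm and 95% v 95%, power is 92.8%; the smallest size that reaches 90% is 37. The stated 40 for 90% power is therefore supported and slightly conservative. With 60 × 0.95 = 57 evaluable per arm, power is 93.4% at -2 points and 89.0% at -3, so both target statements hold under Newcombe.

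**Step 2: other intervals at 60 per arm.**

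| Interval for the difference | 0 points | -2 points | -3 points | Targets (at least 90% at -2, at least 80% at -3) |
|---|---|---|---|---|
| Newcombe hybrid score | 98.9% | 94.7% | 90.9% | met |
| Exact unconditional, score-ordered | 98.7% | 93.9% | 89.6% | met |
| Two Clopper-Pearson limits subtracted, each at 0.025 | 95.4% | 84.0% | 75.7% | missed |
| Exact unconditional, raw difference | 58.5% | 39.5% | 31.5% | missed |

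The last row follows from its threshold. The rule accepts when x - y is at least k, and k must keep the worst-case null error at or below 2.5%. At k = -1 (one success fewer allowed) that error is 2.60%, which is too high; at k = 0 it is 1.67%. Corticotherapy therefore needs at least as many successes as the reference arm.

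**Step 3: decisions on the same data.**

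- 53/60 corticotherapy v 57/60 reference, d = 0.8833 - 0.9500 = -0.0667. Newcombe: Wilson lower limit 0.7782 and upper limit 0.9829, so -0.0667 - sqrt(0.1051² + 0.0329²) = -0.177, noninferior. Clopper-Pearson: 0.7743 - 0.9896 = -0.215, not noninferior.
- 55/60 v 57/60. Newcombe (-13.6%) and Clopper-Pearson (-17.3%) both pass. The raw-difference rule fails, because x - y = -2 is below 0.

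**Step 4: one-sided error at 60 per arm.** Newcombe: 2.45% at 95% v 75%, 2.61% at a reference rate of 90%, 2.67% at 85%, 2.78% at 80%, and at most 2.96% over the whole null. Score-ordered exact: at most 2.41%.

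**The case against.** Four points can be made in the plan's defence.

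- **The exact algorithm is detail for the statistical analysis plan.** That plan is not shown and may name the interval. The sentence applies the formula to the difference between arms, so it does not prescribe a one-sample interval. This stands as far as it goes: it cannot be said that the choice will be made with data in hand. The article is not silent, however. It states one method for sizing and another for analysis without connecting them.
- **Under the most natural good reading there is almost no harm.** The score-ordered exact interval costs 0.2, 0.8 and 1.3 points of power against Newcombe and meets both targets. This stands.
- **The poor rows are weak comparators.** Subtracting two Clopper-Pearson limits is far stricter than a one-sided 97.5% interval: its null error is 0.37% at 75% v 95% and at most 1.2% anywhere. The raw-difference figure is partly an accident of n = 60. At 61 per arm one fewer success is allowed (error 2.48%), and power at no difference becomes 73.8%. This stands in part. Discreteness does not explain the whole loss: allowing one fewer success even at 60 per arm would give only 74.0, 55.0 and 45.9%.
- **An exact interval is a defensible choice.** A reader might infer from the 2.45% error at 95% v 75% that exactness gains nothing here. The calculation does not support that, because Newcombe exceeds 2.5% once the reference rate is somewhat below 95%. With missing values counted as failures, a lower counted rate is plausible.

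**Conclusion.** The mismatch is in the text and concerns the primary decision rule: sizing by Newcombe, analysis by an exact formula that does not identify one interval for a difference. The stated power therefore belongs to a method other than the one stated for analysis. The consequence depends on the reading. It is negligible under a score-ordered exact interval. Under two subtracted Clopper-Pearson limits, power falls to 84.0% at -2 points and 75.7% at -3, below both targets. Under the raw-difference interval it falls to 39.5% and 31.5%.

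A reader might infer that the trial has only about 59% power. The documents do not support this. That figure belongs to one variant the article does not name, at zero true difference, and is partly a discreteness effect. Nor is the sample size wrong, since it reproduces under Newcombe.

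This should be fixed, but it does not undermine the design. The powers assume independent binomial outcomes, 95% reference success and complete data in both arms. They leave out the further loss from counting missing outcomes as failures.

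**What to change.** Before any outcome data are seen, replace the exact binomial wording in Statistical analysis with one named interval for the difference of two independent proportions, and have the sample-size section refer to the same interval. Either of two choices is sound:

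- **Newcombe hybrid-score interval**, as in the sample-size section. The existing power statements then apply. The small price is a one-sided error that can exceed 2.5%, up to 2.96% at 60 per arm.
- **Score-based exact unconditional interval**, with the ordering statistic named. Error stays at or below 2.5%, at about 1 point less power; restate power for 60 per arm (98.7, 93.9 and 89.6%).

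In either case, report a Miettinen-Nurminen score interval as a check, with the decision resting only on the named primary interval. The cost is one line in the analysis section and, for the second choice, a restated power sentence. No patients or additional data are needed.
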